**Ethics and dissemination:**

The study protocol has been approved by the Medical Ethics Review Committee of the Amsterdam University Medical Centers, location AMC (nr. 2020_053). The gathered data and results will be submitted for publication in peer-reviewed journals and spread to coloproctological associations and guidelines.

**Trial registration:**

Dutch Trial Register NL8377. Registered on 12–02-2020.

**Supplementary Information:**

The online version contains supplementary material available at 10.1186/s13063-023-07400-2.

## Significance statement

Haemorrhoidal disease (HD) is a common condition with significant epidemiologic and economic relevance. Until now, there are no large multicentre randomised trials that have studied the difference in effectivity and patient experience between RBL and SCL for the treatment of grade 1–2 HD.

## Introduction

### Background and rationale

Haemorrhoids are a part of normal anatomy, and yet the term haemorrhoids is often used to refer to haemorrhoidal disease (HD) in which clusters of vascular tissue, smooth muscle and connective tissue in the anal canal give rise to symptoms of blood loss, itchiness, soiling and/or prolapse [1]. HD is a common condition with significant epidemiologic and economic relevance. The prevalence of HD rises up to 55% for adults aged between 45 and 65 years of age, with an annual incidence of 5% of the general population [2].

In 1985, Goligher was the first to report a widely accepted grading system for haemorrhoids, which describes four separate groups based on the extent of prolapse inside, or outside, the anal canal [3]. In 460 B.C., Hippocrates described HD with a plethora of treatments, varying from burning, herbs, ligation and surgical excision [4]. Currently, various treatments are available to treat HD [5, 6].

Symptomatic grade 1–2 haemorrhoids can be treated with either rubber band ligation (RBL) or sclerotherapy (SCL) and both treatment options often require multiple sessions [6]. The most common symptom for this patient population is rectal blood loss accompanying defecation [3, 7]. RBL is based on the strangulation and necrosis of haemorrhoidal tissue, resulting in fibrosis and fixation to the surrounding anal mucosa [5, 8]. The most important disadvantages are the feeling of urgency, pain and soiling during and after the procedure. A rare but serious complication of RBL is the occurrence of an arterial bleeding, which in some cases needs to be stopped surgically. On the contrary, SCL induces an inflammation process and local sclerosis of the submucosa which initiates fixation of the haemorrhoidal tissue to the anorectal wall [6, 8]. The haemorrhoid shrinks through the obliteration of the vascular wall. Current literature does not describe major negative side effects, with only a few cases of local infection and haemorrhoidal thrombosis, and very rare complications such as fistula formation and impotence [6, 8]. In the event of haemorrhoidal thrombosis, oral pain medication is usually sufficient; surgical incision of the clot is scarcely required. Another agent that is used in the treatment of HD is phenol. A study showed that it can be equally effective as Aethoxysklerol; however, the use of phenol led to more adverse reactions such as pain, necrosis and ulceration [9].

Furthermore, a recent study has shown a lack of uniformity in the definitions for outcomes, when considering a successful treatment of HD [10]. This results in heterogeneity, limited transparency and hampers the ability to adequately compare results. The most common outcomes in HD studies are pain, blood loss, prolapse and incontinence. Results from a systematic review found no significant difference in the effectiveness of RBL and SCL in treating HD in terms of blood loss, recurrences and complications (73–84% vs 69–88%, 10–18% vs 1.5–29%, and 8–80% vs 34–49%, respectively) [6, 8]. In the present time, similar effectiveness in terms of subjective outcomes (PROMs) and patient experience outcomes, such as satisfaction rates and the subjective experience of a treatment, are important and distinctive measures. These experience measures are scarcely reported in current literature.

In May 2019, the first Core Outcome Set (COS) for HD was developed by the European Society of Coloproctology (ESCP) [11]. The primary outcomes are objective symptoms, complications and recurrences. The patient experience from each treatment will be monitored as a secondary outcome. Symptoms should be scored according to standardized PROMs (blood loss, itchiness, soiling, pain and prolapse). Complications such as incontinence, abscess, anal stenosis and fistula formation need to be reported, together with the recurrence of symptoms (subjective recurrence of disease).

### Objectives

Until now, there are no randomised controlled trials studying the difference in effectivity between RBL and SCL for the treatment of HD. The objective of the THROS trial is primarily to investigate the effectivity of RBL and SCL for patients with grade 1–2 HD in terms of symptom reduction, recurrence and complication rate. Secondary outcomes are patient experience, number of treatments, work leave, crossover rate and subjective symptoms related to recurrence.

## Methods and analysis

### Trial design

The THROS trial is a non-inferiority, multicentre, randomised controlled trial with two parallel groups: RBL vs. SCL. The allocation ratio is 1:1. Crossover is possible for patients who experience no improvement of symptoms after at least two treatments within one treatment arm. It is expected that when two treatments have not reduced symptoms and a third treatment is necessary, both patients and surgeons are inclined to try a new treatment option. So crossover rate is also indicative for treatment success. Also, when patients have a strong preference for one of the two treatment arms and refuse randomisation, then registration in the preference arm is allowed. All patients’ symptoms could not be effectively managed by conservative treatment, which included dietary changes, laxatives, and lifestyle improvements. Conservative management was the first step of therapy in all cases. After eligibility has been established and patients have given their written informed consent, allocation or registration to one of the two treatment arms is possible. Data will be analysed on both ‘intention to treat’ and ‘per protocol’ basis.

The trial was registered at the Dutch Trial Register (NL8377). The protocol was drafted in accordance with the Standard Protocol Items: Recommendations for Interventional Trials statements (SPIRIT) [12].

### Eligibility criteria

#### Inclusion criteria

Grade 1 (symptomatic with rectal blood loss) or grade 2 haemorrhoids (Golligher classification)Aged 18 years old or older and legally competent

#### Exclusion criteria

Grade 3 and 4 haemorrhoids (Golligher classification)Patients that have undergone treatment for HD within the last 12 months, regardless of the type of treatment.

### Interventions

Eligible patients are randomised via Castor^EDC^ to either the SCL or RBL arm. Patients who deny randomisation are eligible to the preference arm of their choice. Patients who are randomised to receive SCL are treated with 4 cc Aethoxysklerol 3% (polidocanol) in the haemorrhoidal tissue via a small 18 mm proctoscope (Sapimed). Patients who are randomised to receive RBL are treated via the same small proctoscope with 3 rubber bands which are placed at the base of the haemorrhoidal tissue (Barron ligation). When after approximately 6–8 weeks a second treatment is required this should be the same treatment as the first (SCL or RBL), after which, in case of persistence after at least two treatments and again 6–8 weeks in between treatments, a crossover is permitted. There are no restrictions regarding concomitant care during the trial.

### Outcomes

#### Primary outcomes

The primary outcome measures are treatment efficacy measured through PROMs according to the ESCP core outcome set of symptom reduction, subjective recurrences and complications (Table 1). The follow-up period for this outcome set is 6 months, and data will be collected at 4 different time points during this period (baseline, 1 week, 6 weeks and 6 months after the first procedure).

**Table 1 Tab1:** Primary and secondary outcome measures

	**Tools of measurement**
**Primary outcomes**	
*Patient-related outcomes*	PROM (minimal score 5, maximum score 25): The lower the score the better the result
- Blood loss	Likert scale – 1 (not at all) to 5 (very much)
- Pain	Likert scale – 1 (not at all) to 5 (very much)
- Prolapse	Likert scale – 1 (not at all) to 5 (very much)
- Itching	Likert scale – 1 (not at all) to 5 (very much)
- Soiling	Likert scale – 1 (not at all) to 5 (very much)
	HISS (minimal score 0, maximum score 20)
- Impact on daily activities	Scale – 0 (no impact at all) to 10 (highly impacted on daily activities)
- Satisfaction with treatment	Scale – 0 (not at all satisfied) to 10 (very satisfied)
*Complications*	
Incontinence	Wexner Fecal Incontinence Score
Abscess	Physical examination^a^
Fistulation	Physical examination^a^
Urine retention	Bladder scan
Anal stenosis	Physical examination^a^
Anal fissure	Physical examination
Arterial bleeding	Physical examination
Thrombosed haemorrhoid	Physical examination
*Recurrence*	Subjective return of initial symptoms

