#### Treatment efficacy

This outcome follows the patient-reported outcome measure-haemorrhoidal impact and satisfaction score (PROM-HISS) questionnaire from the international Delphi procedure of the European Coloproctology group, for which recently the first steps in the validation process were taken [10, 11, 13].

This questionnaire consists of three domains: (1) HD symptoms, (2) impact of HD on daily activities, and (3) satisfaction with treatment [13]. The first domain contains five HD symptoms of which each is scored on a Likert scale ranging from 1 (“not at all”) till 5 (“very much”), resulting in a maximum possible score of 25. During follow-up, any reduction in score on this numeric scale is classified as ‘improvement’. This will then be translated into a binary outcome: “yes” or “no” improvement of symptoms. Both the second and third domains only contain one item, the impact of HD on daily activities and patients’ satisfaction with treatment, respectively. Both are scored on a 10-point numeric rating scale. In respect to the impact of symptoms on daily activities, 0 correlates with “no impact at all” and 10 with “highly impacted on daily activities”. On the contrary, for patient satisfaction with treatment, this ranges between 0 “not at all satisfied” and 10 “very satisfied”. Data from the PROM-HISS questionnaire is collected 1 week after the procedure, so the recall period comprises “the past week” [13].

Complications (i.e. incontinence, abscess, fistula, fissure, urine retention, anal stenosis, arterial bleeding or thrombosed haemorrhoid) are scored at the 6–8 week clinical follow-up appointment at the outpatient clinic. Subjective return of initial symptoms (recurrence) is recorded during the 6-month follow-up period.

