#### Secondary outcomes

Secondary outcome measures consist of patient experience outcomes (PREMs), number of treatments, crossover and number of days on work leave.

Patient experience outcomes are recorded on the PREM questionnaire (Appendix). It contains a series of questions regarding the patients’ experience of the treatment, which is partly scored on a Likert scale ranging from 1 (“not at all”) till 5 (“very much”). Two additional binary (yes/no) questions are added regarding whether patients would undergo the same treatment and whether they would recommend the treatment to acquaintances suffering from similar HD symptoms. The administration of this questionnaire takes place 1 week after treatment. The total number of treatments, the crossover of treatment arms and days of work leave are recorded after a total of 6 months of follow-up. All data entries are stored in Castor^EDC^.

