## Appendix

Patient-reported experience measure (PREM):

1. How much pain did you experience DURING the treatment on a scale of 0 (none) to 4 (very much)?: 0–4
2. How much pain did you experience AFTER the treatment?: 0–4
3. How much feeling of URGE did you experience AFTER the treatment?: 0–4
4. How satisfied were with the treatment on a scale of 1 (very satisfied) to 5 (very unsatisfied)?: 1-5
5. Would you, if necessary, undergo this treatment again?: yes/no
6. Would you recommend this treatment to acquaintances with the same symptoms?: yes/no

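### Table 1 lists a 0–20 HISS score built from two oppositely anchored items with no direction or reverse coding stated, so the total cannot be interpreted as written

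*Protocol article*

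**What the plan says.** Table 1 of the protocol article places two patient-reported scores under primary outcomes. The symptom score runs from 5 to 25 and is stated to be better when lower. The second is "HISS (minimal score 0, maximum score 20", with no direction given. Its two items are impact on daily activities, "Scale – 0 (no impact at all) to 10 (highly impacted on daily activities", and satisfaction with treatment, "Scale – 0 (not at all satisfied) to 10 (very satisfied".

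The Treatment efficacy section describes impact and satisfaction as separate single-item domains and mentions no total. It acknowledges that they run opposite ways: "On the contrary, for patient satisfaction with treatment, this ranges between 0" for the dissatisfied end up to 10 for the satisfied end. No recoding is described there or elsewhere in the article.

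For the PREM, a secondary outcome, the Secondary outcomes section describes a form "which is partly scored on a Likert scale ranging from 1" (not at all) to 5 (very much). The form in the Appendix scores its two pain items and its urge item from 0 to 4, and asks about satisfaction "on a scale of 1 (very satisfied) to 5 (very unsatisfied".

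**The concern.** A score listed as a primary outcome needs a direction. If one item rises as the patient does worse and the other rises as the patient does better, their plain sum measures neither benefit nor harm. A given total could come from a patient who is untroubled and content, or from one who is badly affected and dissatisfied. A treatment that helps on both items would show a weakened difference on the total, or none.

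The PREM text raises a related, smaller risk. Someone who codes or reports the satisfaction item from the article's general description would treat 1 as the unfavourable end, whereas the form makes 1 the favourable end. PREM satisfaction (low is good) also runs opposite to HISS satisfaction (high is good), so two satisfaction measures in one trial need opposite handling.

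The Statistical analysis section adds a reason to state directions. It counts any reduction in a PROM or PREM score as improvement. The rule is worded per symptom, so it may not reach satisfaction at all. If it were applied there, a fall would be a worsening on the HISS item and an improvement on the PREM item.

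**Working it through.** **Inputs.** Impact I: 0 (best) to 10 (worst). Satisfaction S: 0 (worst) to 10 (best). HISS range: 0 to 20. Symptom score range: 5 to 25. All are from Table 1, and the item directions are confirmed under Treatment efficacy.

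**1. Reproducing the stated range.** For the symptom score, five items scored 1–5 give 5 × 1 = 5 to 5 × 5 = 25, so that range is a plain sum. For HISS, I + S gives 0 + 0 = 0 to 10 + 10 = 20, which matches. The reversed form I + (10 − S) gives 0 + (10 − 10) = 0 to 10 + (10 − 0) = 20, which also matches. The range therefore implies a total but does not settle how it is formed.

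**2. What the plain sum measures.**

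| State | I | S | I + S | I + (10 − S) |
|---|---|---|---|---|
| Best | 0 | 10 | 10 | 0 |
| Middle | 5 | 5 | 10 | 10 |
| Worst | 10 | 0 | 10 | 20 |
| No impact, not satisfied | 0 | 0 | 0 | 10 |
| Highest impact, very satisfied | 10 | 10 | 20 | 10 |

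Of the 11 × 11 = 121 possible item pairs, 11 sum to 10, and these run from the best state to the worst. The ends of the plain sum, 0 and 20, are mixed states.

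**3. What happens to a benefit.** Suppose one state is better than another by a points on impact and b points on satisfaction. The plain sum differs by −a + b, and the reversed total by −(a + b).

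- Equal benefit, a = b = 2: plain sum −2 + 2 = 0; reversed total −4.
- Unequal benefit, a = 3, b = 1: plain sum −3 + 1 = −2; reversed total −4.
- Unequal benefit, a = 1, b = 3: plain sum −1 + 3 = +2; reversed total −4.
- Impact 8 and satisfaction 2, against impact 2 and satisfaction 8: plain sum 10 in both; reversed total 8 + 8 = 16 against 2 + 2 = 4.

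The values of a and b are illustrative. Cancellation is complete only when a = b. Otherwise it is partial, and the sign depends on which item moved more.

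**4. Whether the powered comparison uses HISS.** The success definition under Treatment efficacy comes from the five-symptom domain. The sample size rests on 70% success in each arm for symptom reduction, with a 10% limit. With 2.5% in one tail and 80% power, n = (1.960 + 0.842)² × (0.7 × 0.3 + 0.7 × 0.3) / 0.10² = 7.85 × 0.42 / 0.01 ≈ 330 per arm, as stated. No HISS quantity enters.

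**5. PREM, side by side.**

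| Item | Secondary outcomes text | Appendix form |
|---|---|---|
| Pain during, pain after, urge | partly 1–5, not at all to very much | 0–4 |
| Satisfaction | same general description | 1–5, 1 very satisfied, 5 very unsatisfied |
| Two remaining questions | yes/no | yes/no |

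The only 1–5 item on the form does not carry the anchors in the text, so the described scale fits no item.

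**The case against.** The article never says that the two HISS items are added. Reverse coding gives the same 0–20 range, the text presents the items as separate domains, and its authors plainly noticed the opposite directions. How a total is coded could reasonably sit in an analysis plan that is not shown. This stands to the extent that the sum is an inference. It does not remove the problem: the table prints a total over two labelled items, and the labels as printed give it no usable direction. The line above does state its direction.

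Three stronger readings are tempting, and the documents do not support them.

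- A reader might infer that the HISS total would push the trial towards a false finding of non-inferiority whatever the truth. No non-inferiority test or margin is stated for HISS. The 10% limit belongs to the proportion with symptom reduction, and cancellation is complete only for equal changes.
- A reader might infer that a change from baseline in satisfaction is planned, which would have no meaningful starting value. No such analysis is stated, and the baseline entry in Table 2 is for HD symptoms.
- A reader might infer that PREM satisfaction will be analysed in reverse. The text calls the 1–5 scale only part of the form and does not assign it to satisfaction. The form prints its own anchors, and its satisfaction item is internally consistent. The mismatch is real, but a coding error is avoidable by following the form.

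**Conclusion.** The point holds in a limited form. As printed, the HISS total listed under primary outcomes cannot be interpreted: summed as labelled, the best, middle and worst states all score 10, and benefits on the two items offset each other in full or in part. This rests on one assumption, that the items are added without recoding, which the range and the parallel symptom score imply but the article does not state. If satisfaction is in fact reversed, the remaining defect is that neither the reversal nor the direction of the total is given.

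The reach is confined to HISS. The binary symptom-improvement endpoint, the non-inferiority margin and the 330 per arm stand as they are. The PREM mismatch is a secondary inconsistency between the body of the article and its Appendix, on a secondary outcome. Both should be corrected before analysis.

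**What to change.** - **HISS.** Delete the 0–20 total from Table 1 and analyse impact and satisfaction as two separate 0–10 scores, stating that lower is better for impact and higher is better for satisfaction. This agrees with the separate domains under Treatment efficacy. If a total is wanted, define it as impact + (10 − satisfaction), range 0–20, lower is better.
- **PREM.** Align the Secondary outcomes section with the Appendix form: 0–4 for the two pain items and urge, and 1–5 for satisfaction with 1 as very satisfied. State the direction of each item, and note that PREM satisfaction runs opposite to HISS satisfaction.

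The cost is scoring text only. Each item already has its own scale, so no new data are needed, and the sample size does not change.

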## Statistical analysis

Both intention-to-treat and per-protocol analyses shall be carried out. Crossover is not desirable, but possible if deemed necessary by the treating physician. Crossover will be considered as a secondary outcome measure. Analyses will be carried out using SPSS version 26.0. A *p*-value of 0.05 or less is considered as statistically significant.

For the primary outcome, any reduction in a PROM/PREM score per symptom is scored as ‘improvement’ when considering the results as binary success or not. Analysis of primary outcomes will be tested with chi-square test or Fisher’s exact test. Considering there are four time points for the outcomes, these time points will be taken into account during the analysis. Descriptive methods will be used to check the quality of the data, homogeneity of the two treatment groups and primary and secondary endpoints. Significant confounders will be identified using multivariate analysis. Categorical variables will be presented as percentages and continuous variables will be presented as means with their confidence intervals. To examine gender differences, an additional analysis will be carried out. An interim analysis will take place after the first 300 patients have been randomised and 6-month follow-up is completed. Both the number of patients who experienced complications and the number of patients with recurrent symptoms after 6 months will be evaluated between the two groups. If there are significant differences, then the entire study group will discuss these findings and discuss whether the study can be continued.

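### Recurrence, a primary outcome and one of two interim criteria, is defined so that only patients who first improved can have one; if improvement differs between arms, the count can favour the less effective treatment.

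*Protocol article*

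**What the plan says.** The Primary outcomes section of the protocol article lists "symptom reduction, subjective recurrences and complications (Table 1" as the primary set. Table 1 defines recurrence as "Subjective return of initial symptoms". The Treatment efficacy section adds the timing: "Subjective return of initial symptoms (recurrence) is recorded during the 6-month follow-up period". For the symptom score, "any reduction in score on this numeric scale is classified as ‘improvement", which is then turned into a yes/no outcome.

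The Interventions section describes non-response in different words: crossover is allowed "in case of persistence after at least two treatments". No section counts a patient with persisting symptoms as a recurrence, and none states a denominator for recurrence.

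On the interim look, the Statistical analysis section says: "An interim analysis will take place after the first 300 patients have been randomised and 6-month follow-up is completed". Two quantities are then compared, complications and recurrence; for the latter, "the number of patients with recurrent symptoms after 6 months will be evaluated between the two groups". The consequence is: "If there are significant differences, then the entire study group will discuss these findings and discuss whether the study can be continued". Symptom reduction is not among the interim criteria.

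The Abstract and the Discussion both state a non-inferiority hypothesis that names recurrence in its own right. The Sample size calculation gives a 10% non-inferiority limit for symptom reduction only.

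**The concern.** A symptom must first lessen or disappear before it can return. Under the stated definition, the patients at risk of recurrence are those who improved, a group formed after randomisation whose size depends on the treatment. A treatment that helps fewer patients has fewer who can relapse. Comparing the number of recurrences between whole arms therefore mixes two things that pull in opposite directions: how many patients improved, and how many of them relapsed.

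Two uses of the count are at stake. One is a conclusion that sclerotherapy is non-inferior on recurrence, which could be reached because sclerotherapy helped fewer patients. The other is the interim review, where the count is read beside complications alone and a lower figure could be taken as a point in favour of the weaker treatment.

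**Working it through.** **The plan's own figure.** Sample size per arm for symptom reduction, with 70% success in both arms, a 10-point limit, 80% power and 2.5% applied one-sided:

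n = (1.960 + 0.842)² × (0.70×0.30 + 0.70×0.30) / 0.10² ≈ 330 per arm.

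This matches the stated 330. It is sized on symptom reduction, not recurrence.

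**Inputs.** From the protocol: 70% success, 330 per arm at the end, and 300 at the interim with 1:1 allocation, so about 150 per arm. Assumed: 60% or 50% improvement in the weaker arm, and 20% recurrence among improvers in both arms (range 10–30%).

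**Patients not at risk.** With 70% success, 30% of each arm cannot have a recurrence as defined: 0.30 × 330 = 99 at the end and 0.30 × 150 = 45 at the interim.

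**Formulas, per randomised patient.**
- Recurrence = P(improved) × P(recurrence given improved)
- Sustained success = P(improved) × (1 − P(recurrence given improved))
- Failure = 1 − sustained success

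**Results at 20% recurrence among improvers.**

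| Improvement | Recurrence | Sustained success | Failure |
|---|---|---|---|
| 70% v 70% | 14% v 14% | 56% v 56% | 44% v 44% |
| 70% v 60% | 14% v 12% | 56% v 48% | 44% v 52% |
| 70% v 50% | 14% v 10% | 56% v 40% | 44% v 60% |

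In the last two rows the weaker arm has fewer recurrences and more failures. Over 10–30% recurrence among improvers the direction is unchanged: 7.0% v 6.0% up to 21.0% v 18.0% for 70% v 60%, and 7.0% v 5.0% up to 21.0% v 15.0% for 70% v 50%.

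**Break-even.** The recurrence counts are equal when the weaker arm's rate among improvers is 0.70/0.60 = 1.17 times the other's (23.3% v 20%), or 0.70/0.50 = 1.40 times (28% v 20%). Above that ratio the weaker arm shows more recurrences.

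**Non-inferiority on recurrence.** Assume the 10-point limit is also applied to recurrence, with 330 per arm and observed rates equal to those for 70% v 60%.
- Recurrence difference (weaker minus stronger): −2 points. SE = √[(0.14×0.86 + 0.12×0.88)/330] = 0.0262, so the upper 95% limit is −2 + 5.1 = +3.1 points. Non-inferiority would be declared.
- Sustained success difference: −8 points. SE = √[(0.56×0.44 + 0.48×0.52)/330] = 0.0388, so the lower limit is −8 − 7.6 = −15.6 points. Non-inferiority would not be shown.

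For 70% v 50% the corresponding limits are about +0.9 and −23.5 points.

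**Interim, about 150 per arm.** The chance that the recurrence difference reaches two-sided p<0.05 in favour of the weaker arm (2.5% if the arms were equal):
- 70% v 60%: 7.4% at 20% recurrence among improvers, and 5–10% over 10–30%
- 70% v 50%: 18.5% at 20%, and 11–27% over 10–30%

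**The case against.** The strongest reply is that symptom reduction is itself a primary outcome. It is collected from all patients at baseline and three later times, and intention-to-treat analysis is planned. A never-improved patient already counts there as a failure. In the scenarios above, 70% v 60% lies exactly on the 10-point limit, with about a 2.5% chance of passing, and 70% v 50% gives z of about 5.4 at 330 per arm. This stands for the final analysis: a low recurrence count could not by itself carry a claim of equal effectiveness. It does not help at the interim, where symptom reduction is not compared, nor does it repair a separate conclusion on recurrence.

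Second, the definition is brief, and assessors might record anyone with symptoms at 6 months as recurrent. That would shrink the artefact. The article does not say so, and it uses a different word for symptoms that persist.

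Third, the size rests on assumed rates. The protocol plans for equal improvement, under which there is no artefact. Patients who do not improve may also be retreated or cross over, then improve and relapse later, so the one-step model is a simplification. Both points stand. A reader might infer that the count always favours the treatment that fails more often; the documents do not support that, since the direction depends on both the improvement rates and the relapse rates among improvers.

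Fourth, a significant interim difference leads only to discussion, and the chance of a misleading one is modest for a 10-point gap in improvement. This also stands.

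A reader might also take the recording of recurrence at 6 weeks (Table 2) for an error. It is not: the symptom score is taken at 1 week, so a patient can improve by then and relapse by week 6.

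**Conclusion.** The point holds in a limited form. As defined, and with persistence named separately, recurrence can occur only after improvement, so a between-arm count of recurrences can favour the less effective treatment when improvement differs. With assumed improvement of 70% v 60% and 20% recurrence among improvers in both arms, the weaker arm looks 2 points better on recurrence while being 8 points worse on sustained success.

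The exposure lies mainly in two places: the stand-alone non-inferiority hypothesis on recurrence, for which no limit is stated, and the interim look. A reader might go further and conclude that the trial is likely to declare an inferior treatment non-inferior overall. The documents do not support that, because the symptom-reduction outcome would largely reveal a weaker arm at the end.

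**What to change.** At the interim and the final analysis, compare treatment failure at 6 months in all randomised patients. Failure means never improved, or improved and then symptoms returned; its complement is sustained improvement. Say how improvement is judged from the symptom score, and, if a non-inferiority conclusion is to be drawn from this measure, state its limit.

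Keep recurrence as a reported outcome, since the core outcome set described in the Background calls for it, and state its denominator. Do not base a between-arm non-inferiority conclusion, or the interim discussion, on the recurrence count alone.

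The cost is a change of definition and analysis wording. The symptom scores and recurrence status are already collected, so no extra visits are needed. The drawback is small: one redefined comparison that overlaps with the symptom-reduction outcome.
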